#### 2.2.1. Randomized Controlled Trial

The RCT component will include only 60 participants with mild to moderate AD. Forty and twenty participants will be randomly assigned to the verum acupuncture (VA) group and sham acupuncture (SA) groups, respectively. It will be a randomized, assessor- and participant-blinded, sham-controlled trial with a parallel-group design. All trial processes and procedures will be carried out at the Kyung Hee University Korean Medicine Hospital and Korea University Brain Imaging Center (KUBIC) in Seoul, Korea.

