#### 2.12.2. Statistical Analysis for Gut-Brain Axis Indicators

Changes in the gut-brain axis indicators before and after acupuncture will be analyzed within and between groups.

*(1) Gut Microbiota Analysis*. The significance of categorical variables will be determined using the nonparametric Mann–Whitney test for two category comparisons or the Kruskal–Wallis test when comparing three or more categories. Multivariate analyses of variance (PERMANOVA, 999 permutations) with the vegan function Adonis will be performed to test whether community composition is significantly different according to the features associated with sequencing data.

*(2) Serum TARC, ATX Analyzing*. The significance of continuous variables will be determined using the independent two-sample *t*-test or the Mann–Whitney *U* test. The variables will be presented as mean ± standard deviation with 95% confidence intervals.

*(3) fMRI Analysis*. (i) Preevaluation for fMRI session: the between-group and AD severity-dependent differences in interoceptive and exteroceptive properties will be analyzed using mixed-model linear regression and analysis of variance (ANOVA), with the subject as a random factor. Interoceptive and exteroceptive outcomes will be correlated with functional brain activities (voxel-wise beta-series from sensory imagination tasks) and subjective itch and pain ratings of the tasks, which will be performed during fMRI scanning using Pearson's correlation analyses with and without covariates (AD severity, group). If nonparametric data in one or both variables were present, Spearman's rank order correlation will be used. (ii) fMRI data: raw fMRI data will be preprocessed with Analysis of Functional NeuroImages (AFNI, https://afni.nimh.nih.gov) including slice time correction, alignment, registration, masking, smoothing using a Gaussian kernel, and scaling. For the resting-state fMRI signals, the seed-based amplitude of low-frequency fluctuations, functional connectivity, and graph theory analyses will be performed. Task-related BOLD signals will be compared as a function of the four different types of imagination tasks described below using general linear model tests.

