## Figures and Tables

**Figure 1 fig1:**
[figure not shown]
Study flowchart. The light-yellow area depicts the randomized controlled trial component, and the dark-yellow area depicts the cross-sectional component.

**Table 1 tab1:** Study schedule for the AD patient group.

Outcome values and intervention		Baseline assessment	Treatment period								Final assessment
			1-week		2-week		3-week		4-week		
AD symptoms	SCORAD assessment	●				●					●
	EASI assessment	●				●					●
	DLQI assessment	●				●					●

GI symptoms	Abdominal examination	●				●					●
	GSRS assessment	●				●					●
	TDS assessment	●				●					●
	Bristol stool scale	●				●					●
	AR assessment			●	●	●	●	●	●	●	●

Gut-brain axis	BDI STAI-X1, 2	●									
	fMRI image (tasks 1 and 3)	●									●
	Stool collection	●									●
	Blood collection	●									●

	Acupuncture treatment		●	●	●	●	●	●	●	●	

	Investigate for adverse events		●	●	●	●	●	●	●	●	●

BDI, Beck Depression Inventory; STAI, State-Trait Anxiety Inventory; SCORAD, Scoring Atopic Dermatitis; VAS, Visual Analog Scale; EASI, Eczema Area and Severity Index; DLQI, Dermatology Life Quality Index; GSRS, Gastrointestinal Symptom Rating Scale; TDS, Total Dyspepsia Symptom Scale; AR, adequate relief of functional dyspepsia pain and discomfort; AD, atopic dermatitis. Except for the fMRI session, the baseline assessment will take between 30 minutes and 1 hour. An fMRI session, performed at the first and last evaluations, will take about an hour and a half to two hours. Each acupuncture session will take about 15 to 20 minutes. And a total of 30 to 45 minutes will be required for the questionnaires administered in the intermediate and final evaluations. Visit window is ±5 days. Baseline assessment—first acupuncture treatment and eighth acupuncture treatment—Endpoint assessment will be performed within 7 days. The visit window period is ±5 days.

**Table 2 tab2:** Study schedule for the healthy controls.

	Measurements	Assessment	Optional assessment (*n* = 25)
Gut-brain axis	BDI STAI-X1,2	●	
	fMRI image (tasks 1 and 3)	●	
	fMRI image (task 2, *n* = 25)		●
	Stool collection	●	
	Blood collection	●	

BDI, Beck Depression Inventory; STAI, State-Trait Anxiety Inventory. Except for the fMRI session, the baseline assessment will take between 30 minutes and 1 hour. An fMRI session will take about an hour and a half to two hours.

**Table 3 tab3:** Revised STRICTA checklist.

Item	Detail

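### Within-group before-after change in serum and microbiota markers is promised, but only independent-sample tests are named for it, so real changes may be missed

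*Protocol article*

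**What the plan says.** Section 2.12.2 opens with a commitment that covers all gut-brain axis indicators: "Changes in the gut-brain axis indicators before and after acupuncture will be analyzed within and between groups". It then names tests for each type of marker.

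- **Serum TARC and ATX:** "The significance of continuous variables will be determined using the independent two-sample" t-test or the Mann–Whitney U test. The sentence is not limited to between-group use.
- **Microbiota, single measures:** "nonparametric Mann–Whitney test for two category comparisons or the Kruskal–Wallis test when comparing three or more categories".
- **Microbiota, community composition:** "Multivariate analyses of variance (PERMANOVA, 999 permutations) with the vegan function Adonis will be performed". Nothing is said about how permutations treat two samples from one person.
- **fMRI pre-evaluation:** "mixed-model linear regression and analysis of variance (ANOVA), with the subject as a random factor".

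In Table 1 (schedule for AD patients), the rows "Stool collection" and "Blood collection" are each marked at the baseline and final assessments. Section 2.2.1 gives the arm sizes: "Forty and twenty participants will be randomly assigned to the verum acupuncture (VA) group and sham acupuncture (SA) groups, respectively".

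**The concern.** Baseline and final samples come from the same people, so a within-group comparison is a paired comparison. No paired t-test, signed-rank test or mixed model is named for serum or microbiota markers. An analyst who follows section 2.12.2 as written would compare baseline with final values as if they came from two different sets of patients.

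People differ from one another in marker level, and that difference usually persists from one visit to the next. An independent-sample test leaves this stable variation in its standard error, whereas a paired test removes it. The result is a test that is too cautious and can miss a real change.

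Mechanism is the second of the two stated purposes in section 2.1, and the Discussion presents TARC and ATX as mediators linking brain, gut and skin. A missed change could be reported as evidence that these markers do not move.

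**Working it through.** The article gives no error rate, power, correlation or effect size for these analyses, and section 2.2.3 sets the group sizes by expert agreement. There is therefore no planned figure to reproduce. The check shows what the named test does to paired data.

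**Inputs from the article:** n = 40 in the verum arm, with two samples per AD patient.

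**Assumptions (not in the article):** two-sided 5% level; normal data with equal SD at both visits; baseline-to-final correlation ρ of 0.4, 0.6 or 0.8; true shift of 0.4 SD.

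**Step 1: true error rate of the independent test.** The test assumes that the mean difference has variance 2σ²/n. The actual variance is 2σ²(1−ρ)/n. The true two-sided size is therefore 2 × P(Z > 1.96/√(1−ρ)).

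- ρ = 0.4: 1.96/0.775 = 2.53, size 1.1%
- ρ = 0.6: 1.96/0.632 = 3.10, size 0.2%
- ρ = 0.8: 1.96/0.447 = 4.38, size under 0.01%

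**Step 2: power of the independent test.** The standardised shift is 0.4 × √(40/2) = 1.789, so power is P(Z > (1.96 − 1.789)/√(1−ρ)) = P(Z > 0.171/√(1−ρ)).

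**Step 3: power of the paired t-test.** The effect size is dz = 0.4/√(2(1−ρ)), evaluated with the noncentral t distribution on 39 degrees of freedom.

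| ρ | Independent test | dz | Paired test | Share of power lost |
|---|---|---|---|---|
| 0.4 | 41% | 0.365 | 61% | 20/61 ≈ one third |
| 0.6 | 39% | 0.447 | 79% | 40/79 ≈ one half |
| 0.8 | 35% | 0.632 | 97% | 62/97 ≈ 64% |

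**Step 4: simulation at other values.** With n = 40 and ρ of 0.3, 0.5 and 0.7, the simulated size was 0.020, 0.007 and 0.0004 for the independent t-test, and 0.021, 0.008 and 0.0005 for Mann–Whitney. The nonparametric option therefore does not help. The paired t-test stayed close to 0.05. Simulated power for a 0.5 SD shift, paired against independent t:

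- n = 40: 0.74 vs 0.62, 0.87 vs 0.63, 0.98 vs 0.67
- n = 20 (sham arm): 0.44 vs 0.32, 0.57 vs 0.29, 0.78 vs 0.25

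**Step 5: between-arm use.** An independent t-test on change scores, verum against sham, kept its size in simulation (0.0535). The named test is sound there.

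**The case against.** Every named test has a proper use in this design. A change score is one value per participant, so a two-sample t-test or Mann–Whitney test of change between verum and sham is valid. Kruskal–Wallis fits the three-group microbiota comparison described in the Discussion. One can read section 2.12.2 as naming the between-group tests and leaving the within-group test to a fuller plan. The error is also conservative, the study is declared non-confirmatory (sections 2.2.3 and 2.11), and a within-arm change does not isolate an acupuncture effect as the verum-sham contrast does.

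Most of this stands, and it limits the point to the within-group half. It does not remove the point. The section itself announces a within-group analysis and then says, without qualification, how significance will be determined for the serum markers. It names a subject-level method for the fMRI pre-evaluation but none for serum or microbiota. On either reading, the announced within-group analysis has no suitable test.

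Three stronger readings are tempting, and the article does not support them.

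- **Inflated false positives between arms.** This would arise if both visits were pooled as independent observations in a verum-sham test. No section says that they will be.
- **PERMANOVA with free permutation across visits.** The article states the number of permutations and the function. It neither says that permutation is unrestricted nor assigns the method to a time effect.
- **Loss of most of the power.** Under the assumptions above, the loss is a third at ρ = 0.4 and a half at ρ = 0.6. It exceeds half clearly only towards ρ = 0.8.

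**Conclusion.** The point holds for within-group change in TARC, ATX and single microbiota measures such as alpha diversity. The tests named for them are unsuitable for paired data and err in one direction: they reject too rarely. The calculated range depends on the assumed correlation and shift, since the article supplies neither. If the correlation were near zero, the two approaches would perform almost alike; the stronger it is, the greater the loss.

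Between-group comparisons of change with the named tests are valid and are not criticised. Severity is moderate: the analyses are exploratory and no sample size rests on them, but they bear on a stated purpose of the trial, and the correction needs no new data.

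**What to change.** In section 2.12.2:

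1. For within-group change in TARC, ATX and alpha diversity, name a paired t-test or Wilcoxon signed-rank test, or a mixed model with subject as a random factor as in the fMRI pre-evaluation.
2. Limit the two-sample t, Mann–Whitney and Kruskal–Wallis tests to between-group comparisons with one value per participant.
3. If PERMANOVA is used for a time effect, state that permutations are restricted within participant.
4. As an optional improvement, compare verum with sham by ANCOVA of the final value on baseline. With equal SDs, the change score has variance 2(1−ρ)σ² and the adjusted value (1−ρ²)σ², a ratio of (1+ρ)/2. That is 0.7, 0.8 and 0.9 of the change-score variance at ρ = 0.4, 0.6 and 0.8. The change-score test is valid, only less efficient.

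The cost is a few lines of analysis wording, settled before unblinded data are analysed. Samples, visits and group sizes do not change.

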## 1. Introduction

Atopic dermatitis (AD) is a relapsing and remitting, inflammatory, chronic skin disease that is characterized by severe itching and eczema [1]. Its prevalence varies widely according to geographic location, but according to an International Study of Asthma and Allergies in Childhood (ISAAC)-based report, it is on the rise worldwide, with a global prevalence of approximately 230 million [1, 2]. Additionally, the factors involved in AD pathophysiology are complex and diverse, and recent focus has mainly been on the hygiene hypothesis, loss-of-function mutations of the FLG-encoding gene, environmental factors, and the gut microbiota-skin axis [3].

However, AD cannot be cured [3]. Therefore, multistep guidelines have been outlined to control symptoms and maintain remission for as long as possible. However, in clinical practice, many patients do not respond properly to existing treatments. Persistent, recurring skin symptoms also exist because of treatment discontinuity. On the other hand, if continuous systemic treatment is administered, concerns about side effects and complications come to the forefront [4]. Therefore, to cope with the limitations of these existing treatments, the potential role of East Asian medicine, including Korean medicine, is being actively studied [5, 6]. A recent paper reported that acupuncture is a safe AD treatment that can be effective at improving itchiness, Eczema Area and Severity Index (EASI) scores, and other global symptoms [6].

Our research team has conducted previous randomized controlled trials (RCTs) addressing AD-related topics [7, 8]. Thirty-eight patients with AD were recruited, divided into two groups, and treated with verum or sham acupuncture twice a week for 4 weeks. In that study, acupuncture was performed on three fixed acupoints (ST36, LI11, and PC6 bilaterally) and two additional points. Additional points were selected on an individualized basis according to the accompanying symptoms, such as ST43 and GB41 for gastric stiffness and tenderness or LI2 and GB31 for diarrhea and constipation. Through this study, we not only confirmed the effectiveness of acupuncture treatment but also highlighted two notable implications. The first was that AD severity and the presence of gastrointestinal (GI) symptoms were positively correlated, and the second was that some patients exhibited clear improvements, but some patients did not.

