#### 2.2.2. Cross-Sectional Component

The cross-sectional component will include 40 healthy controls and 60 patients with AD. The study will be conducted at the Kyung Hee University Korean Medicine Hospital and KUBIC.

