### 2.6. Randomization and Allocation Concealment

Participants who meet the criteria and sign a consent form will be randomly assigned. Block randomization will be conducted to form the verum acupuncture (VA) and sham acupuncture (SA) groups at a ratio of 2 : 1, and the specific randomization method will proceed as follows.

An independent statistical expert will generate a random number table using random allocation software (SAS 9.2 (PROC PLAN, SAS Institute Inc., Cary, NC, USA)). This random number table will be sent to administrative staff at the Acupuncture and Meridian Science Research Center (AMSRC), who are not involved in assessing or recruiting the participants. The staff will place each random number in a sealed, opaque envelope and store them. After the screening, the investigator will contact the administrative staff by e-mail or phone, and the personnel will immediately forward a document that contains the group allocation and participant's unique random number. The investigator will keep this e-mail in the trial master file in printed form.

There will be no randomization of the 40 healthy controls. Only 25 of them can volunteer for fMRI Task 2, which will be conducted on a first-come, first-served basis.

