#### 2.11.3. Gut-Brain Axis Indicators

*(1) Fecal Sampling and Microbiota Analysis Protocol*. For each participant, approximately 200 mg of fecal samples will be employed as an input for DNA extraction with the FastDNA for the fecal kit (MP Bio, Santa Anna, CA, USA) following the manufacturer's instructions. The V3-V4 hypervariable regions of the 16S rRNA gene will be targeted using a universal primer set (5ʹ-CCTACGGGNGGCWGCAG and 5ʹ-GACTACHVGGGTATCTAATCC) with sequencing barcodes. Sequencing will be performed on an Illumina MiSeq platform with 2 × 250 bp paired-end protocol yielding pair-end reads. We mainly follow the QIIME2 pipeline [8] for bacteria profiling based on 16S rRNA. DADA2 will be selected as a tool for sequence quality control, and the EzTaxon [9] database will be chosen as the taxonomic reference database. The results will be imported into the *R* statistical environment (The *R* Foundation, https://cran.r-project.org/) for further analysis using the Bioconductor package phyloseq [10]. Alpha-diversity will be determined by the value of clustered observed operation taxonomic units (OTUs), Shannon index, and the inverse Simpson index. Beta diversity will be assessed using weighted or unweighted UniFrac distance matrices.

*(2) Blood Sampling and Analysis of TARC and ATX*. Blood samples will be collected in the blood collection room on the second floor of Kyung Hee Medical Center. After clotting, the serum will be separated by centrifugation at 3000 rpm for 10 minutes and stored at −80°C. Analysis of TARC and ATX will be conducted using commercial ELISA kits at the AMSRC.

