Therefore, in this study, we will confirm the activity of each region and the linkage through fMRI as the main indicator of the gut-brain axis. The difference in brain activity between patients with AD and healthy individuals is actively studied [28, 29], and our study will also investigate changes in activity before and after acupuncture. Additionally, the diversity of the gut microbiota and the dominant strain in AD patients have been discussed [39, 40]. In our study, the gut microbiota of the VA treatment group, the SA treatment group, and healthy controls will be compared. Moreover, as mediators connecting the brain and gut, hematologic indicators, TARC and ATX, will be measured together. Effector/memory CD4+ T cells play an important role in allergic diseases. TARC is produced in the intestinal endothelium and epithelial keratinocytes and is known to play a key role in the development and activation of Th2-type inflammatory mediators as well as inducing T-cell chemotaxis [41]. ATX is known to exhibit high mRNA activity in the brain, adipose tissue, ovaries, and small intestine [42], and it has been shown to cause pruritogenic-mediating activity through an ATX-lysophosphatidic acid signaling process in animal studies [43]. Based on these observations and facts, TARC and ATX will be evaluated as mediators that connect the brain, intestine, and skin. The collection and evaluation of these multifaceted data is an advantage of this study.

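### A significant Adonis PERMANOVA is to be read as a composition difference, but with unequal groups it can also be driven or masked by unequal within-group spread

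*Protocol article*

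**What the plan says.** Section 2.12.2 (1) names the test, "Multivariate analyses of variance (PERMANOVA, 999 permutations) with the vegan function Adonis", and says that it "will be performed to test whether community composition is significantly different according to the features associated with sequencing data". Section 2.11.3 supplies the distances: "Beta diversity will be assessed using weighted or unweighted UniFrac distance matrices".

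The main group sizes are fixed and unequal. Section 2.2.1: "Forty and twenty participants will be randomly assigned to the verum acupuncture (VA) group and sham acupuncture (SA) groups, respectively". Section 2.6 confirms the 2:1 allocation: "Block randomization will be conducted to form the verum acupuncture (VA) and sham acupuncture (SA) groups at a ratio of 2 : 1". Section 2.2.2: "The cross-sectional component will include 40 healthy controls and 60 patients with AD". The Discussion adds that "the gut microbiota of the VA treatment group, the SA treatment group, and healthy controls will be compared", which makes a 40/20/40 comparison.

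The article states no significance level, effect size or expected dispersion for this test. It does not say that any group is expected to vary more than another in its microbiota.

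**The concern.** The question asked is about location: do the groups differ in their typical community? The reference distribution from permuted labels assumes more than equal location. It treats the labels as fully exchangeable, so the null is that the groups share both centre and spread. The pooled pseudo-F also weights the two variances differently in its numerator and denominator when group sizes differ. A difference in spread can therefore raise the statistic with no shift present, or lower it when a shift is present.

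At stake is the interpretation of a named mechanistic outcome. A significant PERMANOVA would be reported as a composition difference although it might reflect one group being more heterogeneous. A non-significant one might hide a shift if the larger group is the more heterogeneous.

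**Working it through.** **Inputs from the article.** VA 40, SA 20 (2.2.1); AD 60, healthy 40 (2.2.2); three-group comparison 40/20/40 (Discussion); 999 permutations (2.12.2). The plan gives no figure to reproduce.

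**Assumed.** Level 5%; SD ratio between groups from 1 to 2; Euclidean space with 10 independent normal features. UniFrac itself was not simulated, because it needs a phylogeny that the article does not give.

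**Statistic.** With k groups and N samples, pseudo-F = [(SST − SSW)/(k − 1)] / [SSW/(N − k)]. SST is the sum of all squared pairwise distances divided by N. SSW is the same sum within each group divided by its size, added over groups.

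**Why spread matters.** For two groups with equal centroids, per dimension:
- expected numerator = (n2·σ1² + n1·σ2²)/N
- expected denominator = [(n1 − 1)σ1² + (n2 − 1)σ2²]/(N − 2)

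The permutation reference has a ratio near 1. With a 1.5-fold SD (variance 2.25) in one group:
- 40:20, smaller group wider: (20 + 40×2.25)/60 = 1.833; (39 + 19×2.25)/58 = 1.409; ratio 1.30.
- 40:20, larger group wider: (20×2.25 + 40)/60 = 1.417; (39×2.25 + 19)/58 = 1.841; ratio 0.77.
- 60:40, smaller group wider: (40 + 60×2.25)/100 = 1.750; (59 + 39×2.25)/98 = 1.497; ratio 1.17.
- 60:40, larger group wider: (40×2.25 + 60)/100 = 1.500; (59×2.25 + 39)/98 = 1.753; ratio 0.86.
- 30:30: (30 + 30×2.25)/60 = 1.625; (29 + 29×2.25)/58 = 1.625; ratio 1.

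**Simulated rejection, identical centroids** (999 permutations, 1000 runs per cell, Monte Carlo standard error about 0.007 at 0.05):

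| Sizes | Equal spread | Smaller group 1.25 / 1.5 / 2 times SD | Larger group 1.25 / 1.5 / 2 times SD |
|---|---|---|---|
| 40:20 | 0.047 | 0.083 / 0.184 / 0.279 | 0.023 / 0.005 / 0.003 |
| 60:40 | 0.053 | 0.073 / 0.112 / 0.163 | 0.034 / 0.015 / 0.007 |

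Equal sizes (30:30 and 50:50) stayed at 0.045–0.056 whatever the spread. At 40/20/40 (600 runs) the level was 0.053 with equal spread. With 1.5 times the SD it was 0.185 for SA alone, 0.023 for healthy alone, and 0.087 for VA and SA together.

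**Dependence on dimension.** A smaller repeat at 40:20 with SA 1.5 times wider rejected 12%, 18% and 22% at 5, 10 and 20 dimensions.

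**Power.** For a fixed centroid shift, with the variance of the mean difference held constant, power at 40:20 was 0.69 with equal spread, 0.40 with the larger group 1.5 times wider and 0.86 with the smaller group wider. At 60:40 it was 0.75, 0.62 and 0.83.

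**Bounded distance.** For Bray–Curtis on 40-part Dirichlet data with the same mean composition and concentration 30 versus 15 (400 runs), PERMANOVA rejected:
- 40:20: 0.42 (smaller group wider) or 0.09 (larger group wider)
- 60:40: 0.66 or 0.42
- 50:50: 0.52–0.59

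Imbalance is therefore not the only route by which spread drives rejection.

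**Welch-type alternative.** In the Euclidean model a Welch-type distance statistic held about 4–7% in all these unequal-size settings, with negligible power loss under equal spread. On Bray–Curtis Dirichlet data of the same kind (equal mean composition, twofold concentration difference) it rejected in 19% to 71% of runs, depending on group sizes and on which group was wider.

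**The case against.** **Scope.** This is a condensed article, and a dispersion check is the sort of detail left to a full protocol or analysis plan that is not shown. That stands: its absence is not the finding. What remains is that the article fixes both the test and an unqualified reading of it. The study is declared non-confirmatory, which limits the consequence but does not make the reading correct.

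**Certainty.** A reader might infer that the planned test will reject or miss because of spread. The documents do not support this. They give no dispersions, and with equal spread the level is right at both ratios.

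**False positives in the randomised contrast.** A reader might also take the 40:20 inflation as a false-positive rate for VA versus SA. Under no treatment effect of any kind, randomisation makes those labels exchangeable and the type I error exact. A systematic difference in spread after treatment would itself be an effect, though not a shift.

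**Heterogeneous response.** The Introduction reports that "some patients exhibited clear improvements, but some patients did not", and it is tempting to conclude that VA will be the more dispersed arm and that a real shift will probably be missed. That sentence concerns clinical improvement in an earlier trial, not microbiota. An SD ratio of 1.5 means 1.5² = 2.25 times the variance; if response were independent of baseline, treatment would have to add 125% of the existing between-person variance. The article predicts nothing of the kind.

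**Not every contrast is unequal.** VA 40 versus healthy 40 is balanced, and the within-group before–after comparisons use the same participants.

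**Model.** The figures come from Gaussian Euclidean data, vary with dimension, and are not UniFrac results. They show direction and order of size only.

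**Conclusion.** The point holds as a conditional one about interpretation. A significant Adonis result cannot on its own be attributed to a composition shift, because the permutation null covers spread as well as centre.

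If dispersions differ by an SD ratio of 1.25 to 1.5, the size is as follows:
- **AD versus healthy (60:40):** about 7–11% rejection with equal centroids when healthy controls are more dispersed, and about 1.5–3% when patients are. Nothing in the design secures equal spread here, so this is where a false claim about centroids mainly arises.
- **VA versus SA (40:20):** about 8–18% at 10 dimensions (somewhat more at 20) when SA is more dispersed, and about 0.5–2% when VA is. The problem is misattribution and lost power (0.69 to 0.40 in the example), not type I error under no effect.

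These figures rest on the assumed level, SD ratios and Euclidean model. Neither the presence of unequal spread nor its direction can be established from the documents.

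**What to change.** In 2.12.2 (1), for each between-group PERMANOVA, run betadisper with permutest on the same UniFrac matrix and state a reading rule in advance. Attribute a significant result to a composition shift only when dispersions do not differ materially; otherwise report a difference in composition, dispersion or both. Judge the dispersion result by its size as well as its p-value, since with 20 to 60 per group a non-significant test does not show equal spread.

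For the unequal-size contrasts, add a Welch-type distance permutation test as a sensitivity analysis. It should not be the sole basis for a claim, because with a bounded distance it too can reject on spread alone.

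The cost is a few lines of R on matrices already planned, with no new data. Some significant results will carry a more cautious interpretation.

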### 2.4. Eligibility Criteria

#### 2.4.1. Inclusion Criteria

*(1) Healthy Group*
Men and women aged 19 to 49 years able to read and write the Korean languageBody mass index (BMI) of 18.5 or more and less than 25 (kg/m^2^)Right-handedDo not have AD diagnosed in accordance with the Hanifin and Rajka criteria [11].Agreement with the study protocol and providing written informed consent

*(2) AD Patient Group*
Men and women aged 19 to 49 years able to read and write the Korean languageBody mass index (BMI) of 18.5 or more and less than 25 (kg/m^2^)Right-handedAD diagnosed in accordance with the Hanifin and Rajka criteria [11].Scores from 10 to 40 points of the objective Scoring Atopic Dermatitis (SCORAD) scaleAgreement with the study protocol and providing written informed consentDo not participate in other clinical studies in the preceding month

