### 2.5. Participant Recruitment

We will recruit 60 patients with AD and 40 healthy controls. Recruitment will mainly proceed via bulletin board posts in the hospital. We plan to also postannouncements in nearby town offices and campuses.

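### The AD-versus-healthy comparison is non-randomised with no stated matching, and the only tests named for serum and univariate microbiota measures cannot adjust for age or sex

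*Protocol article*

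**What the plan says.** **The contrast.** Section 2.2.2: "The cross-sectional component will include 40 healthy controls and 60 patients with AD". The Abstract lists fMRI, gut microbiota, serum TARC and serum ATX among the indicators of this cross-sectional study. The Discussion (section 3) plans a microbiota comparison across the verum, sham and healthy groups. Table 2 shows that controls give blood and stool once.

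**How the groups arise.** Section 2.6: "There will be no randomization of the 40 healthy controls". Section 2.5: "We will recruit 60 patients with AD and 40 healthy controls", and "Recruitment will mainly proceed via bulletin board posts in the hospital", with town offices and campuses added. These channels are given once, for both groups. No matching rule and no age or sex quota is stated.

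**Shared entry limits.** Section 2.4.1 opens both lists alike: "Men and women aged 19 to 49 years able to read and write the Korean" language. Both lists also require BMI from 18.5 to below 25 and right-handedness. The exclusion list in 2.4.2 is not split by group; it removes smokers and recent users of antibiotics or probiotics, among others.

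**Tests.** Section 2.12.2, on serum: "The significance of continuous variables will be determined using the independent two-sample" t-test or the Mann–Whitney U test. On microbiota: "nonparametric Mann–Whitney test for two category comparisons or the Kruskal–Wallis test when comparing three or more categories", plus PERMANOVA with terms not named. The fMRI pre-evaluation and the task ratings use mixed-model regression and ANOVA, and BOLD signals use general linear models. The only covariates named in the section are AD severity and group, for the fMRI correlations.

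**The concern.** Randomisation makes an unadjusted t-test or rank test valid for verum versus sham. It gives no such protection to patients versus volunteers. Section 2.12.2 does not separate the two contrasts, so for serum and single microbiota measures the same unadjusted tests would serve both.

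The shared limits narrow the differences between the groups, but ages may still range over 30 years and sex is unrestricted. If an indicator varies with age or sex and the groups differ in either, the test picks up that difference and the report attributes it to AD. The gut-brain mechanism is the second of the two objectives in 2.1, and the healthy controls are recruited for it.

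**Working it through.** **What the plan gives.** Group sizes of 40 verum, 20 sham and 40 healthy, so 40 + 20 = 60 AD against 40 healthy. Section 2.2.3 sets these from earlier studies' sizes and expert agreement, with no effect size, SD, significance level or power. No stated figure for this contrast can be reproduced. The article also gives no expected age or sex distribution, so the inputs below marked as assumed are assumptions, including the two-sided 5% level.

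**Step 1. Precision of the unadjusted comparison.** In SD units of the indicator,

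SE = √(1/60 + 1/40) = √0.0417 = 0.204.

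The difference detectable with 80% power is (1.96 + 0.842) × 0.204 = 0.57 SD.

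**Step 2. Spurious difference from age.** With no true AD effect, bias b = (age gap in SD) × (age–indicator correlation). The chance of a significant result is

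Φ(−1.96 + b/SE) + Φ(−1.96 − b/SE).

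| Assumed age gap | Assumed correlation | b (SD) | b/SE | False-positive rate |
|---|---|---|---|---|
| 0.25 SD | 0.2 | 0.05 | 0.24 | 6% |
| 0.5 SD | 0.3 | 0.15 | 0.73 | 11% |
| 0.8 SD | 0.4 | 0.32 | 1.57 | 35% |

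**Step 3. Spurious difference from sex.** Here b = (sex effect in SD) × (difference in sex proportion). Assumed effects of 0.3 to 0.8 SD and imbalances of 10 to 30 percentage points give b from 0.3 × 0.1 = 0.03 to 0.8 × 0.3 = 0.24 SD, and false-positive rates of 5% to 22%.

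**Step 4. Both together, with and without adjustment.** A simulation of 10,000 trials had no true AD effect. It assumed mean ages of 31.5 (AD) and 26.5 (healthy), 60% against 40% of one sex, 0.3 outcome units per 7 years of age, 0.5 units for sex and residual SD 0.9. The unadjusted t-test rejected in 35.7% of runs; linear regression on group, age and sex rejected in 5.1%.

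The formula is for a two-group comparison of means. For the rank tests it is a guide to size, not an exact value.

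**The case against.** **The serum sentence names no groups.** Section 2.12.2 opens with changes before and after acupuncture. Controls have a single assessment, so for change scores the between-group comparison can only be verum versus sham, where these tests are valid. This stands as a limit on the quotation: that serum patients-versus-controls data fall under it is an inference. The inference is sound, because the Abstract places serum TARC and ATX in the cross-sectional study, controls give blood for no other stated purpose, and no other serum test is offered.

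**Covariate lists are commonly left to an analysis plan.** This also stands in part. A reader might infer that all gut-brain comparisons are unadjusted two-group tests. The article does not support that: the fMRI measures, task ratings and PERMANOVA use models that can carry covariates, and silence about age and sex there is not an error. The point rests on the serum and univariate microbiota tests, where the article fixes methods that cannot adjust.

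**The design already limits confounding.** True. The common limits on age, BMI and handedness, and the common exclusions for smoking and recent antibiotics or probiotics, matter for these measures. BMI, held within a window of 6.5 kg/m², is the weakest of the obvious candidates. Age within 19–49 and sex remain.

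**No imbalance is shown.** A reader might infer that one group will come more from campuses and so be younger. Section 2.5 gives the same channels for both groups, so that has no support. Similar groups would leave little bias; the named tests could not correct it if they differ.

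**The study is not confirmatory** (2.2.3, 2.11). That bears on how much weight a p-value carries. It does not remove bias from the estimate.

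**Conclusion.** The point holds for the baseline AD-versus-healthy comparison of serum TARC, serum ATX and single microbiota measures. That contrast is planned and non-randomised, has no stated matching, and is served only by tests that cannot adjust for age or sex. The randomised verum-versus-sham comparison is unaffected.

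The size depends wholly on assumed imbalances. For age alone, a nominal 5% error rate becomes about 6% to 35%, with 11% in the middle case. At the low end the problem is negligible. The age and sex biases above, taken singly, lie below the 0.57 SD that the comparison could detect with 80% power. Age and sex differences acting in the same direction could be material.

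**What to change.** In 2.12.2, add a rule for the baseline AD-versus-healthy contrast only:

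- Analyse serum TARC, serum ATX and the univariate microbiota measures by regression on group, age and sex, on the log or rank scale if skewed. BMI is optional.
- Enter the same terms before group in PERMANOVA and include them in the AD-versus-healthy fMRI and rating models.
- Keep the t-test, Mann–Whitney and Kruskal–Wallis results as descriptive for this contrast, and leave them as they are for verum versus sham.

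**Cost.** Two degrees of freedom for age and sex, three with BMI, out of 100 participants. No new data are needed: age and BMI are established at eligibility (2.4.1), and sex decides which task videos a participant sees (2.11.3).

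Precision need not suffer. With an age gap of 0.5 SD, adjustment inflates the variance by 1 + 0.6 × 0.4 × 0.5² = 1.06. A correlation of 0.3 reduces the residual variance by the factor 1 − 0.3² = 0.91. The SE then changes by √(1.06 × 0.91) = 0.98, which is no loss.
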